# Primary care implementation study to scale up early identification and brief intervention and reduce alcohol-related negative outcomes at the community level (PINO): study protocol for a quasi-experimental 3-arm study

**DOI:** 10.1186/s12875-021-01479-9

**Published:** 2021-07-01

**Keywords:** Scaling-up, Implementation, Primary healthcare, Hazardous alcohol use, Harmful use of alcohol, Heavy drinking, Training and support, Community action, EIBI

## Abstract

**Background:**

Primary healthcare-based Early Identification and Brief Intervention (EIBI) for hazardous and harmful alcohol use is both a clinically relevant and cost-effective strategy to reduce heavy drinking. Unfortunately, it remains poorly implemented in daily practice. Multiple studies have shown that training and support (T&S) programs can increase the use of EIBI. Nonetheless, gains have only been modest and short-term at best. Suggestions have been made to rely more on multicomponent programs that simultaneously address several barriers to the implementation of EIBI. The PINO-project aims to evaluate the added value of such a multicomponent program to improve EIBI delivery in daily practice.

**Methods/design:**

A quasi-experimental three-arm implementation study in Flanders (Belgium) will assess the effects of tailored T&S to General Practitioners (GPs) with or without community mobilisation on EIBI delivery in general practice. The study lasts 18 months and will take place in three comparable municipalities. In municipality 1 and 2, GPs receive a tailored T&S program. The T&S is theoretically founded and tailored to the GPs’ views, needs and practice characteristics. Furthermore, community actions will be embedded within municipality 1 providing additional, contextual, support. In municipality 3, GPs are offered a minimal intervention to facilitate data collection.

The primary outcome is the proportion of adult patients screened for hazardous and harmful alcohol use at the end of an 18-month implementation period. The secondary outcome is the scaling up activity at municipal level in screening rates, as assessed every 3 months, and the proportion of patients who received an additional brief intervention when necessary. Furthermore, the correlation between the opinions and needs of the GP’s, their practice organisation and their EIBI performance will be explored.

**Discussion:**

The PINO-project addresses the gap between what is theoretically possible and the current practice. This is an innovative study combining T&S at GP level with community actions. At the same time, it implements and evaluates practice T&S based on the theoretical domains framework.

**Trial registration:**

This trial was approved by the Ethics Committee for Research of UZ/KU Leuven (reference number s63342 and G-2020-2177-R2(MAR)) and is registered on clinicaltrials.gov (NCT04398576) in May 2020.

**Supplementary Information:**

The online version contains supplementary material available at 10.1186/s12875-021-01479-9.

## Background

Harmful alcohol consumption is one of the leading risk factors for poor health and death in the world. About 6% of all-cause mortality is attributable to alcohol, which is equivalent to 2.8 million deaths worldwide [1]. In Belgium, 21% of men and 7% women display a hazardous or harmful drinking behaviour [2]. Alcohol-related harm transcends the individual as it also affects families, communities, and health systems [3].

Reducing harmful and hazardous alcohol consumption could have a major impact on lowering the disability-adjusted life years [4]. The majority of alcohol-related health problems occurs in the middle-aged population, suggesting that preventive measures will benefit most when directed at this population [5, 6].

Early Identification and Brief Intervention (EIBI) has been shown to be a cost-effective method to reduce the number of heavy drinking patients in primary care [7]. Interestingly, the highest efficacy occurs when brief advice is delivered to non-treatment-seeking, hazardous drinking patients [8, 9]. Even though EIBI in primary healthcare was found to be effective, and general practitioners (GPs) recognize that primary healthcare is an important and appropriate setting for delivering EIBI, implementation of EIBI is generally lacking [10]. Considerable effort has been invested in identifying barriers to explain this observation [11, 12]. Lack of resources, workload, and absence of Training and Support (T&S) are identified as the main implementation barriers, whereas adequate resources and training are considered the main facilitators [13]. The evaluation of different strategies addressing these barriers with a view on improving implementation of EIBI by GPs yielded only modest results [14].

Previous strategies that aimed to upscale EIBI delivery in general practice remediated only a limited number of barriers and relied on a one-size-fits-all approach [15]. Such a basic approach is likely to be ineffective in the highly variable and complex context of general practice, which is marked by differences in practice organisation, personal needs, believes and attitudes [16]. Multicomponent programs, adapted to the needs and concerns of both GPs and the general population, regarding alcohol-related EIBI implementation is advised [17–19]. Public health interventions directed at the general population, the so-called ‘community actions (CAs)’, are considered essential to facilitate EIBI delivery in general practice [20]. CAs have been suggested to reframe the public’s and professionals’ views on alcohol use [20]. Unfortunately, to date, integrating such CAs to facilitate EIBI delivery has only generated limited attention [20].

T&S have been found to increase EIBI rates for GPs who feel confident and are committed to work with at-risk drinkers. Training programs can significantly improve providers’ knowledge, self-efficacy, and expectations about the value of EIBI [21–23]. However, it does not affect less secure or motivated GPs to the same extend [18]. These findings underline the need to address GPs’ attitudes, needs and views towards working with at-risk drinkers in training and support programs. Customising support with personal experiences should motivate GPs and create opportunities to scale up EIBI-performance [24, 25]. Furthermore, compatibility with the actual practice activity should be considered [26], including timing and the choice of innovation steps [24].

Poor sustainable results in implementing EIBI might also be due to the lack of a sound theoretical implementation model. Currently, the most comprehensive model is the Behavioural Change Wheel (BCW) linked to the Theoretical Domains Framework (TDF). The TDF provides a comprehensive assessment of the factors that are likely to influence practitioners’ target behaviour [27]. Furthermore, the TDF can be used as a theoretical model to address the barriers and facilitators for EIBI delivery in general practice by its mapping of related behavioural changes techniques [12].

## Aim and objectives

The PINO-project, which stands for Professional Involvement to reduce alcohol Negative Outcomes, aims to scale up the use of EIBI for hazardous and harmful alcohol use in general practice. This study is based on the hypothesis that training and supporting GPs, tailored to their beliefs, attitudes, and working context, together with community mobilisation may improve their EIBI performance. The PINO-project has the following objectives:
To implement and evaluate a multicomponent program comprising tailored T&S and CAs to increase the delivery of EIBI in general practice over an 18-month period.To study the added value of integrating CAs within the strategy to improve EIBI delivery in general practice.To monitor individual GPs’ progression on EIBI delivery for hazardous and harmful alcohol use on a 3-monthly basis and evaluating the effect of scaling up activities on municipal level (e.g., tailored support, CAs).To assess EIBI performance at practice level in relation to the characteristics of GPs and their practice organisation, the changes in GPs’ beliefs and attitudes and the provided support.

## Methods

### Study design and setting

The PINO-study consists of a quasi-experimental three-arm implementation study in three comparable medium-sized Flemish (Belgium) municipalities [28]. All three municipalities have a multicultural population with around 80,000 to 100,000 inhabitants. In addition, they are all marked by a large student population due to the presence of universities or university colleges [28].

#### Municipality 1

Intervention area where GPs receive T&S embedded within a community mobilisation program.

#### Municipality 2

Intervention area where GPs receive T&S without CA.

#### Municipality 3

Support As Usual (SAU) area where GPs receive a minimal intervention that comprises an overview of the current guidelines and knowledge.

During an 18-month implementation period, GPs in the T&S area’s will receive personalised support linked to an online evaluation of their needs, views, practice organisation and EIBI-performance. This on a three-monthly base (Fig. 1).

**Fig. 1 Fig1:**
[figure not shown]
Timeline of the study

### Outcomes

The primary outcome comprises the overall early identification-rates of GPs during the 18-month period, specified per municipality. This is the proportion of the consulted adult patients (> 18 years) attending general practice for any reason, which were questioned about their alcohol consumption over an 18-months period at area level.

The early identification rates will be measured as follows:
**Numerator:** Patients (> 18 years) attending general practice for any reason who are questioned about their alcohol consumption during the study period of 18 months per area.**Denominator:** Number of unique patients (> 18 years) attending general practice during the 18 months study period per area.

Secondary outcomes will be related to personal views, as measured using the TDF domains, to practice organisation and to provided support. These secondary outcomes comprise (a) the cumulative early identification rates and (b) the cumulative brief intervention rates.

#### Cumulative early identification rate

The proportion of patients that visited the general practitioner’s office for any reason that were questioned about their alcohol consumption at 3, 6, 9, 12, 15 and 18 months after baseline at area level:
**Numerator:** Patients (> 18 years) attending general practice for any reason that were questioned about their alcohol consumption during the periods 0–3, 0–6, 0–9, 0–12, 0–15 and 0–18 months per area.**Denominator:** Number of unique patients (> 18 years) attending general practice during the periods 0–3, 0–6, 0–9, 0–12, 0–15 and 0–18 months per area.

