#### Handling of missing data

If a GP withdraws from the study prematurely, all data collected until that point will be analysed (using the intent-to-treat approach). No additional data will be collected after withdrawing from the study.

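### The 3-monthly outcomes are defined only over overlapping cumulative windows, which can mask gradual waning and dilute the effect of a booster or community action in its own quarter

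*Protocol article*

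**What the plan says.** The Abstract (Methods/design) gives the 3-monthly series its purpose: "The secondary outcome is the scaling up activity at municipal level in screening rates, as assessed every 3 months". Objective 3 under Aim and objectives is "To monitor individual GPs’ progression on EIBI delivery for hazardous and harmful alcohol use on a 3-monthly basis", together with evaluating scaling-up activities such as tailored support and community actions. The motivation, in the Abstract's Background, is that with earlier training programmes "gains have only been modest and short-term at best".

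The outcome itself, under Cumulative early identification rate, is the proportion of visiting patients "questioned about their alcohol consumption at 3, 6, 9, 12, 15 and 18 months after baseline at area level". It has as numerator the patients "questioned about their alcohol consumption during the periods 0–3, 0–6, 0–9, 0–12, 0–15 and 0–18 months per area" and as denominator "Number of unique patients (> 18 years) attending general practice during the periods 0–3, 0–6, 0–9, 0–12, 0–15 and 0–18 months per area". The cumulative brief intervention rate uses the same six windows. No rate is defined for a separate quarter.

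Under Statistical analysis plan, the primary rate is modelled by linear regression with intervention group as a factor and a random effect for practice. Secondary outcomes are to be analysed in the same way. No time term or arm-by-time term is stated.

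On GPs who leave early, Handling of missing data says that "all data collected until that point will be analysed (using the intent-to-treat approach"), and that nothing is collected afterwards.

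**The concern.** The trial wants to know whether screening is built up and kept up. A cumulative window answers a different question: how many attenders have been questioned at least once so far. A patient questioned in month 2 counts in all six results. Screening can decline quarter by quarter while the reported rate still climbs, and a response to the booster sessions (months 6 and 9) or to a community action is averaged with everything before it. Fitting a group-only model to such windows compares accumulated totals between arms and does not test a time course. The last window, 0–18 months, has the same numerator and denominator as the primary outcome and so adds no information.

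Withdrawal raises a related matter of observation time. The primary rate is defined over 18 months, but a GP who leaves at month 6 supplies a 6-month rate, and no adjustment for the shorter window is stated.

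**Working it through.** The plan gives no figure for the time course, re-attendance or GP withdrawal, so there is no figure of its own to reproduce here. The check is an illustration on assumed inputs.

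**Assumptions.** Per 1,000 patients on a GP's list, the quarterly attendance probability is 0.9, 0.5 or 0.15 in shares of 30%, 40% and 30%. Uniform attendance of 0.4 and of 0.7 gives the range. In each quarter a stated proportion s of not-yet-questioned attenders is questioned.

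**Formulas.** For a patient with attendance probability a, after quarter t:
- ever attended = 1 − (1 − a)^t
- ever questioned = 1 − Π(1 − a·s_j), j = 1 to t
- cumulative rate = sum of ever questioned / sum of ever attended
- quarterly rate = newly questioned in the quarter / attenders in the quarter (515 per 1,000 in the mix)

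**1. Waning: s = 12, 9, 6, 4, 2, 1%**

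| Month | Questioned so far | Attended so far | Cumulative rate | Quarterly rate |
|---|---|---|---|---|
| 3 | 61.8 | 515.0 | 12.0% | 12.0% |
| 6 | 104.4 | 680.2 | 15.3% | 8.3% |
| 9 | 131.0 | 765.5 | 17.1% | 5.2% |
| 12 | 148.1 | 818.4 | 18.1% | 3.3% |
| 15 | 156.4 | 854.4 | 18.3% | 1.6% |
| 18 | 160.5 | 880.6 | 18.2% | 0.8% |

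The month-18 cumulative rate is 13.5% with attendance 0.4 and 21.8% with 0.7. The reversed pattern (1% rising to 12%) ends at the same value in each case: 18.2%, 13.5% and 21.8%.

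**2. Dilution of a quarter's effect.** With s = 6% throughout, 116.3 patients are questioned by month 12, of whom 27.3 in months 9–12. Suppose activity doubles in that quarter alone, after the 9-month booster. The quarterly rate goes from 27.3/515 = 5.3% to 54.6/515 = 10.6%, a ratio of 2. The cumulative rate goes from 116.3/818.4 = 14.2% to (116.3 + 27.3)/818.4 = 17.5%, a ratio of 1.23.

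**3. Complete stop: s = 6% for two quarters, then none.** Cumulative: 6.0, 8.9, 7.9, 7.4, 7.1, 6.9%. The numerator freezes at 60.5 while new attenders enter the denominator, so a stop is visible.

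**4. Withdrawal.**
- Constant s = 6%: a GP's own rate is 8.9% if the window closes at month 6 and 19.0% at month 18 (7.4% v 14.2% with attendance 0.4; 9.0% v 22.7% with 0.7). The short window gives about 40–52% of the full one. If 20% of GPs leave at month 6, the area rate is (0.8 × 167.6 + 0.2 × 60.5)/(0.8 × 880.6 + 0.2 × 680.2) = 17.4% instead of 19.0%, with no change in screening behaviour.
- A GP who questions 20% of attenders in the first quarter, then stops and withdraws at month 3, counts at 20.0%. Followed to month 18 with no more screening, the rate would be 103.0/880.6 = 11.7%.

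The two cases move the rate in opposite directions.

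**The case against.** The outcome is openly labelled cumulative, and its last point must equal the primary. A reader might go further than the point made here and infer that the trial cannot tell whether screening has stopped. The documents do not support that. With 960 attenders per GP per quarter and 20% new each quarter (assumed), screening 20% in the first two quarters only gives 20, 33, 29, 25, 22, 20%, while screening 20% in the last two only gives 0, 0, 0, 0, 11, 20%. The end values coincide, but the curves do not. Even the waning series above flattens. The raw material for quarterly rates is also planned: patients seen in the past 3 months per practice and GP (Clinical audit data), and a 3-monthly dataset of EIBI counts per GP (Online GP enquiry). The gap is in the outcome definition, not in data collection.

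That part stands. It does not dispose of the point, because the shape of the curve is not what the stated analysis examines, and a rising or level cumulative rate is easily read as sustained activity.

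A reader might likewise infer that the withdrawal rule breaches intention-to-treat or inflates the intervention arms' rates. Neither follows. Keeping withdrawn GPs in their area and using all their data is compatible with intention-to-treat, and the bias can run either way. If withdrawal were equal across arms, a proportional shift would largely cancel in the relative risk that the plan reports. What remains is that a truncated window is treated as an 18-month one.

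**Conclusion.** The point holds as a mismatch between purpose and outcome definition. As written, the 3-monthly series can rise by about 6 points (12.0% to 18.2%) while quarterly screening falls below 1%, and a doubling of activity in one quarter can appear as a ratio of 1.23. These sizes rest on assumed attendance and screening patterns; across the attendance assumptions tried, the waning series ends between 13.5% and 21.8%, always above its 12.0% start. The mechanism needs only nested windows. Gradual waning and quarter-specific effects are masked; a complete stop is not. The primary outcome's definition and the sample size are not affected.

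The withdrawal issue is secondary. Its direction depends on how leavers screen, and its size is unknown because no withdrawal rate is given.

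**What to change.** - Make secondary outcome (a) the rate in six non-overlapping quarters: patients questioned in the quarter over patients seen in that quarter, each patient counted at most once per quarter.
- Analyse it with arm, quarter and arm-by-quarter terms and a practice random effect, with GP nested within practice if each GP contributes repeated quarters.
- Keep the cumulative curves as descriptive, and note that the 0–18 value is the primary outcome.
- Let withdrawn GPs contribute the quarters observed. Describe the withdrawal rule as analysis of all observed data by allocated area, not as full 18-month follow-up.

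The cost is wording and one model; the 3-month attender counts and EIBI counts are already planned. Quarterly rates will be noisier than cumulative ones. If patients are rarely questioned twice, the quarterly rate also drifts down slightly under constant effort, since those already questioned stay in the denominator (6.0% to 4.9% over six quarters in the constant case above). It should therefore be read mainly as a contrast between arms within a quarter.

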#### Cumulative brief intervention rate

The proportion of patients (> 18 years) screening positive for hazardous or harmful alcohol use that received oral brief advice/intervention and/or were referred to a digital-based system for advice and/or were referred to another healthcare provider during the periods 0–3, 0–6, 0–9, 0–12, 0–15 and 0–18 months after baseline at area level.
**Numerator:** Number of unique patients (> 18 years) that received oral brief advice/intervention and/or were referred to a digital-based system for advice and/or were referred to another healthcare provider during the periods 0–3, 0–6, 0–9, 0–12, 0–15 and 0–18 months per area.**Denominator:** Number of unique patients (> 18 years) screening positive for hazardous or harmful alcohol use as assessed for 0–3, 0–6, 0–9, 0–12, 0–15 and 0–18 months per area.

### Recruitment and eligibility criteria

All GPs within the three municipalities will be addressed systematically through the local GP associations by means of a standard information letter. In addition, a researcher will personally contact the GPs by telephone for clarifying the project and providing reminders. Both GPs and GP trainees will be invited to participate. GPs will be eligible for inclusion if they can read and understand Dutch, and if they work in a general practice within one of the three included municipalities.

GPs sign an ICF specifying their agreement to participate in all trainings, answer the needed online questionnaires and record screening and advise activities in e-forms. E-forms are electronic forms, integrated in the Electronic Health Records (EHR) of GPs. They are developed to record EIBI delivery, diagnosis and referral. There will be no remuneration provided for the work as it is consistent with regular quality practice. All included practices will need to display a poster in the waiting room, indicating their participation in the study. The poster explains that the practice is taking part in a study that evaluates anonymized data from patient records for scientific purposes. Patients may oppose to being included in the study upon simple request.

### Interventions

#### Minimal intervention

All GPs in the comparator group (municipality 3) will receive an information package containing the most current recommendations by the Flemish GP association concerning harmful and hazardous alcohol use [29]. These recommendations include the guidelines of the Superior Health Council of Belgium^1^ regarding responsible alcohol use, i.e., an acceptable weekly intake of maximum 10 units of alcohol per week with a least two alcohol-free days [30]. The package also comprises educationally conceived practice tools for EIBI, referral strategies to specialised services or internet support about EIBI and links to online documentation.

#### Training and support

The T&S provided in this study will be facilitated by a team of researchers with both international and local experience related to alcohol use in general practice. The trainers are affiliated with the faculty of medicine from the KU Leuven and have an active role in vocational training and continuing medical education for GPs and GPs in training.

##### Training

At the start of the study, GPs in municipality 1 and 2 will receive a standardised educational training based on the TDF-concepts to increase capability, motivation and opportunities for the delivery of EIBI. Here, the differences in practice organisation will be emphasized. Two booster sessions will be planned at 6 and 9 months after baseline (Table 1). These booster sessions will provide support based on changes in the TDF domains, grouping GP in relevant homogenous groups. Due to the SARS-CoV-2 pandemic, a fully online blended learning training package was designed comprising two preparatory online e-learning modules followed by two livestream sessions. If possible, the booster sessions will be performed face to face.

**Table 1 Tab1:**
[figure not shown]
SPIRIT flowchart

*CA* community actions, *EIBI* Early Identification and brief interventions, *EHR* electronic health record

Personalisation of the training package will be established by assessing changes in capability, motivation, believes and practice organisations of the participating GPs. Therefore, standardized online inquiries [31] and active interaction during the livestream sessions will be used. The content of each training is based on previously conducted studies on the subject matter [32, 33] and have been piloted in training practices outside the intervention areas. The training sessions will aim to encourage experience-based reflection related to EIBI delivery, GP’s attitudes and highlights practice organisation. During these sessions, skills will be practiced and reflections on how to implement EIBI in relation to practice characteristics will be stimulated. Further, task definition and delegation of possible tasks, management of EHR and other features of practice organization and collaborative care will be emphasized during these training sessions. Importantly, this training package combines theory and practical exercises facilitated by acknowledged and experienced trainers.

